## Abstract

**Background:**

Mental health conditions affect one in seven young people and research suggests that current mental health services are not meeting the needs of most children and youth. Learning health systems are an approach to enhancing services through rapid, routinized cycles of continuous learning and improvement. Patient-reported outcome measures provide a key data source for learning health systems. They have also been shown to improve outcomes for patients when integrated into routine clinical care. However, implementing these measures into health systems is a challenging process. This paper describes a protocol for a formative evaluation of the implementation of patient-reported measures in a newly operational child and adolescent mental health centre in Calgary, Canada. The purpose is to optimize the collection and use of patient-reported outcome measures. Our specific objectives are to assess the implementation progress, identify barriers and facilitators to implementation, and explore patient, caregivers and clinician experiences of using these measures in routine clinical care.

**Methods:**

This study is a mixed-methods, formative evaluation using the Consolidated Framework for Implementation Research. Participants include patients and caregivers who have used the centre’s services, as well as leadership, clinical and support staff at the centre. Focus groups and semi-structured interviews will be conducted to assess barriers and facilitators to the implementation and sustainability of the use of patient-reported outcome measures, as well as individuals’ experiences with using these measures within clinical care. The data generated by the patient-reported measures over the first five months of the centre’s operation will be analyzed to understand implementation progress, as well as validity of the chosen measures for the centres’ population.

**Discussion:**

The findings of this evaluation will help to identify and address the factors that are affecting the successful implementation of patient-reported measures at the centre. They will inform the co-design of strategies to improve implementation with key stakeholders, which include patients, clinical staff, and leadership at the centre. To our knowledge, this is the first study of the implementation of patient-reported outcome measures in child and adolescent mental health services and our findings can be used to enhance future implementation efforts in similar settings.

**Supplementary Information:**

The online version contains supplementary material available at 10.1186/s12961-024-01174-y.

## Background

It is estimated that one in seven young people experience a mental illness and that about 70% of mental health challenges have their onset before the age of 18 [1, 2]. Anxiety disorders are the most common of these disorders affecting five percent of Canadian children aged 5–17 years old while 2.1% reported a mood disorder in 2019 [3]. Mental illness is one of the leading causes of disability among adolescents [1]. Despite the burden of mental health conditions in children and adolescents, data suggests that current mental health services are not meeting the needs of a majority of these children and youth. Only 44.2% of children experiencing a mental health condition received any services, revealing a large gap in services for children and youth mental health [4]. In Alberta, a Western Canadian province, the rates of emergency department visits for pediatric mental health concerns increased 35% between 2010 and 2020 [5], likely the result of a lack of availability of services for urgent mental health needs in the community [6]. The COVID-19 pandemic has further amplified the critical need for adequate mental health supports and services for children and youth [7, 8].

To address the needs of children and youth in Alberta, a new centre for children and adolescents with urgent mental health concerns, called “The Summit: Marian & Jim Sinneave Centre for Youth Resilience” (herein, The Summit) is opening in March 2023 in Calgary, Canada. The City of Calgary is located in the province of Alberta and is Canada’s third largest municipality, serving 1.3 million people [9]. The Summit will support children and youth (0–18 years old) with acute mental health concerns in a community setting. The centre will be operated by Alberta Health Services (AHS), the province-wide, publicly-funded health system in Alberta, Canada. The Summit has an integrated research program in partnership with the University of Calgary. This close partnership between academic researchers and the health system is supporting the development of The Summit as a learning health system (LHS).

As defined by Menear et al. (2019), an LHS is a “*dynamic health ecosystem where scientific, social, technological, policy, legal and ethical dimensions are synergistically aligned to enable cycles of continuous learning and improvement to be routinised and embedded across the system, thus enhancing value through an optimised balance of impacts on patient and provider experience, population health and health system costs*.” AHS is facing rising health care costs and is therefore moving towards a model of Value-Based Health Care (VBHC), where the purpoted aim is to offer patients the best possible outcomes weighed against the cost of providing services [10, 11]. The implementation of a LHS is seen as a pathway towards operationalizing VBHC and thus, establishing a LHS has become a priority for AHS [12].

Foundational to a LHS is the rapid executing of learning cycles, where data are generated within clinical practice and transformed to knowledge and that knowledge is rapidly applied back into clinical practice [11]. A key source of data in a learning health system is patient-reported outcomes (PROs), gathered with patient-reported outcome measures (PROMs). PROMs are validated questionnaires filled out by the patient about their health status, quality of life, or well-being [13]. PROMs provide valuable data about outcomes from the patient’s perspective that can be used within an LHS to answer questions regarding treatment effectiveness, disease trajectories, and the value of care provided [14]. PROMs also provide valuable information for the clinician and patient’s own learning, for example, whether a particular treatment is having the intended effect on a patient’s symptoms. The use of PROMs in routine clinical care can improve communication between patient and clinicians, enhance share-decision making, self-management and patient outcomes [15, 16].

Despite the value of PROMs within a health system, their successful implementation into routine clinical care is complex [17, 18]. It requires a significant investment of time and resources, as well as the development of a supportive information technology infrastructure [17, 19]. Commonly cited challenges to their implementation include finding appropriate PROMs (i.e., relevant to patients’ needs, feasible to use, and adding value to the clinical encounter), designing PROMs data collection processes around clinical workflows, getting buy-in from clinical staff, and creating a culture that is supportive of learning and quality improvement [17]. In child and youth mental health care, there are additional challenges, including finding PROMs that have been validated for their use in children and youth, developing data collection platforms and workflows that allow the collection of responses from both parents and children [20, 21]. There are also additional ethical questions to navigate, such as whether the youth, one caregiver, both parents or all should be responding to PROMs, whose responses will be more strongly weighted, whether a parent should respond to a PROM about their child without their child’s consent, and at what age a child has the right to keep their PROMs data private from their caregivers [21–23].

PROMs will be embedded into routine clinical care processes at The Summit when it opens. At the initial stages, the focus on PROMs will be their use as an intervention to enhance learning for the patient and clinician about the patients’ function and responses to treatment. PROMs data used for learning at the meso and macro levels will begin once sufficient data are collected for planned research projects and quality improvement, although the success of these activities will depend on the quality of PROMs data that is collected. Given the complex interactions between technical, organizational, personal and familial factors that may impact how effectively PROMs are collected and used for individual and family clinical care, it is crucial to assess and address unidentified or unresolved barriers to effective implementation in order to be successful in the implementation of PROMs at The Summit. The assessment will inform refinements to the components of the PROMs intervention and the implementation strategies, optimizing PROMs data collection and clinical use at the centre.

### Purpose

This paper describes a protocol for the formative evaluation of the implementation of PROMs for clinical care within The Summit. The purpose is to optimize the collection and use of PROMs. The evaluation objectives are to:Assess the implementation progress to date (penetration, fidelity, appropriateness, and adoption)Identify barriers and facilitators to implementation and sustainability of PROMs at The SummitExplore patient, caregivers and clinician experiences of PROMs in clinical care

### Context

The Summit is a stand-alone facility which aims to serve children and youth ages 0–18 years old with emerging or worsening mental health concerns. It will have three main services: (1) a walk-in service for urgent mental health concerns; (2) a day program to support youth transitioning from a hospital admission back to their home; and (3) intensive community treatment services, designed to prevent the need for hospitalization, which provides youth with escalating mental health concerns with short-term, intensive therapy, consisting of group, family and individual therapy, and psychiatry services.

In partnership with researchers at the University of Calgary, The Summit has an embedded, patient-oriented research program with three functions: (1) generating new knowledge from data collected from patients at The Summit; (2) testing new interventions for children and youth with depression and anxiety; and (3) implementing and evaluating effectiveness of interventions that are not widely available to children and youth in Calgary. Additionally, the socioeconomic (i.e., cost-effectiveness and policy) impact of the interventions offered will be assessed.

### Intervention description

Measurement-Based Care (MBC) is a commonly used term to describe the routine clinical use of PROMs in mental health services [22]. It is accepted that MBC consists of three main steps: (1) administering a symptom, outcome, or process measure (i.e., PROM) ideally before a clinical encounter; (2) clinician and patient review of PROM data; (3) collaborative re-evaluation of the treatment plan informed by data [24].

MBC will be a standard part of care at The Summit. Three PROMs will be administered across all services at the Centre, the acute version of the Pediatric Quality of Life Inventory Generic Core Scales (PedsQL), the Revised Children’s Anxiety and Depression Scale (RCADS-25), and Columbia-Suicide Severity Rating Scale (C-SSRS). These measures were chosen based on the International Consortium for Health Outcomes Measurement’s Set of Patient-Centered Outcome Measures for Children and Young People with Anxiety and Depression, including OCD and PTSD, informed by the PROMs available within the provincial electronic health record (EHR), and in collaboration with patients, caregivers, and researchers [25].

The acute version of the PedsQL is a 23-item questionnaire with a 7-day recall period. It has 4 scales (physical, emotional, social, school functioning) and three summary scores (Physical Health Score, Psychosocial Health Score and Total Scale Score) [26]. It has self-report forms for children in 3 different age groups and parent-report forms for 4 different age groups [26]. RCADS-25 is a 25-item questionnaire for children and youth ages 8–18 with 2 subscales (anxiety and depression) and a total scale score which can be converted to norm-based T scores [27]. It has self-report and parent-report forms. The C-SSRS is a 7-item self-report questionnaire for youth ages 10 and older, which classifies individuals as high, moderate or low risk for suicide [28]. The RCADS-25 and C-SSRS have demonstrated good reliability and evidence of their validity in pediatric mental health populations [27, 28]. The reliability and validity of the PedsQL in this population has not been reported, however in the general population it performs well and is widely used within Alberta’s pediatric health system [29].

Figure 1 illustrates PROM data collection timepoints for each service. For walk-in services, PedsQL will be administered routinely at intake, with the intake process flagging whether RCADS and C-SSRS need to be administered. For the 2-week day hospital program, all three PROMs will be administered at intake and at discharge. For intensive community treatment services, the three PROMs will be administered at intake, midpoint of treatment (after 2 weeks) and at discharge. In each case, the PROMs will be automatically scored and represented graphically (along with prior PROM scores) in a downloadable summary document which also contains patients’ responses to each item. The summary document will be imported into the patients’ EHR by the intake coordinator for the service. During the clinical encounter, the clinician will access patient scores in the EHR and review them with the patient. Together they will discuss patient concerns highlighted by the PROM and re-evaluate the treatment plan. Whenever possible, PROMs will be administered to both patients and caregivers. A clinician-reported measure, the Children’s Global Assessment Scale (CGAS), will be also be collected at each PROM collection timepoint in the day program and intensive community treatment services, as it is part of the standard of care for children and youth mental health services in Alberta [30].

**Fig. 1 Fig1:**
[figure not shown]
Patient-reported outcome measures in the three services at The Summit

### Implementation process

The implementation of PROMs at The Summit was guided by the Quality Implementation Framework (QIF) [31]. The QIF is an implementation process model which was designed to guide the “how-to” processes of implemenation [31]. It has 14 steps divided into four phases: (1) Initial considerations regarding the host setting, (2) Creating a structure for implementation, (3) Ongoing structure once implementation begins, (4) Improving future applications [31].

We formed a MBC working group consisting of operational leadership and academic partners (clinical and health systems researchers) 18 months prior to the opening of The Summit. The working group assessed the context; adapted the MBC intervention to The Summit; developed the information technology structure to collect, use and record PROMs in the patient EHR; and designed the implementation approach. The implementation strategies were developed based on existing PROMs implementation guidelines [24, 25, 32, 33]. We engaged youth and caregivers through The Summit’s advisory councils in designing the PROMs processes, selecting the PROMs to use and informing the implementation strategies.

Once an opening date for The Summit was finalized, an implementation team was created, consisting of two clinical leads from The Summit and 4 researchers. The implementation team finalized the PROMs clinical workflows and created a detailed plan for implementation. Once The Summit opens and PROMs collection begins, onsite technical and clinical support will be offered through the implementation team.

This formative evaluation is part of phase three of the QIF. We used the Implementation Research Logic Model (IRLM) to specify the core elements of the implementation design [34]. The IRLM for this project details the determinants, strategies, proposed mechanisms of change and outcomes for the MBC implementation project and is available as supplementary online material (Supplementary File 1).

## Methods

### Design

This study is a convergent mixed-methods, formative, implementation and progress-focused evaluation [35, 36]. This type of formative evaluation occurs during the implementation phase and focuses on identifying and resolving factors affecting implementation, as well as assessing progress towards the desired outcomes [35]. We will use the Consolidated Framework for Implementation Research (CFIR) to guide a comprehensive and systematic exploration of the factors affecting implementation of MBC at The Summit [37]. CFIR offers a menu of constructs that could influence implementation efforts, organized in five domains, some with subdomains: Innovation domain (i.e., MBC); Outer setting domain (i.e., the health system, academic institutions and community services surrounding The Summit); Inner setting domain (i.e., The Summit); Individuals domain (i.e., the roles and characteristics of The Summit staff, implementation team, and PROMs working group); Implementation process domain (i.e., implementation strategies, see Supplementary File 1) [37]. A detailed evaluation plan is included as supplementary material (Supplementary File 2). This study protocol was approved by The University of Calgary Research Ethics Boards (REB22-1137). Figure 2 illustrates the study design. A populated SPIRIT checklist has been included as supplementary material (Supplementary File 3) [38].

**Fig. 2 Fig2:**
[figure not shown]
Study design flowchart

### Participants and recruitment

The MBC program will begin collecting PROMs data at The Summit opening (March 2023). Recruitment and data collection specific to this evaluation (surveys, interviews, focus groups) will begin three months after The Summit opens in order for staff and patients to develop a comprehensive experience of MBC. Sample sizes are based on feasibilty of recruitment and estimates to reach saturation point where no new information is forthcoming.

*Patients and caregivers* We will recruit 12–16 individuals ages 12–18 years old who accessed services at The Summit between March 2023 and August 2023 and have engaged in MBC (i.e., completed PROMs on 2 or more occasions). We will recruit 12–16 caregivers of patients (not necessarily paired with the patient participants) who accessed services at The Summit between March 2023 and August 2023 and who have been engaged in MBC (i.e., completed PROMs on two or more occasions).

A consent to be contacted for research purposes will be included within the PROMs data collection platform for each of the three services. Patients and caregivers who consent to be contacted for research will be approached for participation in focus groups. For day-program and intensive community treatment services, patients and caregivers will also be asked whether they consent for their PROMs data and clinical EHR data to be used for research. Patients accessing walk-in services may be in crisis, therefore it would not be appropriate to ask for consent to use data for research at the time of their visit, however they will be asked for consent to be contacted for research, and their consent to participate will be sought at a later date.

*The Summit staff* All Summit staff will be invited to participate in a survey through an email from The Summit staff members on the implementation team. For the interviews, staff will be invited to participate voluntarily through the survey, as well as purposively sampled to ensure a recruit a diverse sample representing healthcare professionals (e.g., social workers, psychologists, psychiatrists, psychiatric nurses), administrative support staff and leadership from across the three services.

### Data collection

All data will be stored on secure servers at the University of Calgary.

*Staff surveys (month 3–4)* The survey will be administered online with a mix of closed and open-ended questions about acceptibility, appropriateness, feasibility and fidelity, as well as general attitudes towards MBC at The Summit. The survey will be customized for each role (clinician, support staff, leadership).

*Staff interviews (months 4–6)* Semi-structured interviews will be conducted with 8–12 staff members to understand their attitudes towards and experiences with MBC at the Centre, and barriers and facilitators to implementation of MBC. Clinicians will also be asked about the appropriateness of the PROMs (i.e., PedsQL, RCADS-25, C-SSRS) and how scores are represented in the summary score sheet, and how they are using PROMs within clinical encounters (to assess fidelity). CFIR will inform the development of the interview guide.

*Patient and caregiver focus groups (months 4–6)* Focus groups will be held with patients and caregivers to understand their experiences with measurement-based care. Between 2–3 focus groups with 4–8 individuals will be held for both patients and caregivers, separately. The focus group interview guide will focus on usability of the platform, appropriateness of the PROMs, fidelity (are PROMs being discussed within their encounters), and perceptions of MBC as a part of their clinical care.

*Electronic Health Record Data (month 5)* De-identified patient data from the electronic health records of all patients attending The Summit will be acquired 5 months into operation. This will include the total number of patient encounters at the centre, the number of patients who have the PROMs summary document in their EHR (by service), and the number of patients who have the PROMs summary document at intake, midpoints of treatment and discharge.

*MBC PROMs database (month 5)* PROMs data collected through MBC from patients and caregivers consenting to data use for research will be matched with demographic and clinical data extracted from patients’ EHR (i.e., diagnosis, co-occurring diagnoses, sex and gender, language spoken at home, health care provider professional designation, number of episodes of care, types of therapeutic services accessed, clinician-reported measure scores, ethnicity including Indigeneity). Data will be acquired for the period of time from the start of operations to five months post The Summit’s opening. These data will be analyzed to understand penetration (e.g., proportion of patients filling out PROMs at planned timepoints, demographic and clinical characteristics of patients responding to PROMs) and appropriateness of measures (e.g., percentage of missing responses, associations between PROMs and with clinician-reported outcomes).

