### Data analysis

*Qualitative data* Qualitative data sources include open-ended survey questions, interviews with clinical staff and focus group data. We will initially use a deductive, directed content analysis approach, as described by Hsieh and Shannon (2015), guided by CFIR, to analyze barriers and facilitators to implementation [39]. To provide a more in-depth description of patient and caregiver experiences with and perceptions of MBC, as well as clinical staff’s experiences (separately) a second analysis of qualitative data will be performed using inductive, conventional content analysis [39]. Qualitative data analysis will be performed using NVIVO qualitative data analysis software [40].

*Staff survey data* Descriptive statistics will be calculated for demographic and closed-response questions from the survey.

*De-identified EHR data* To specifically examine penetration of the intervention in The Summit, the percentage of patients participating in MBC (i.e., filling out PROMs) will be calculated using the total number of patients enrolled in the services compared with the number of patients who responded to PROMs. The percentage of patients filling out PROMs at intake, midpoint and discharge will also be calculated (as a measure of fidelity and penetration).

*PROMs data* The PROMs data of those who consented to research use will be used to perform subgroup analyses by service (i.e., walk-in, day program, intensive community treatment) and by patient demographics (e.g., age, sex, gender, spoken language, education level).

To examine the validity of the chosen PROMs for use in MBC in this population, analyses of item quality, construct validity and responsiveness (ability to capture change) will be performed on the PROMs data of those who consent for their data to be used. Item analysis will be performed by calculating descriptive statistics for the individual items in each PROM will be calculated (median of the responses, the frequency of endorsement, i.e., the proportion of people choosing each response option, and non-response rates i.e., percent of missing data). Construct validity of the PROMs will be evaluated using a hypothesis-testing approach recommended by the COSMIN group [41]. Responsiveness of the measures will be evaluated using Guyatt’s responsiveness ratio [42].

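### The all-patient penetration figure counts summary documents imported into the EHR but is reported as patients filling out PROMs, so a completed but unimported PROM reads as non-completion

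*Protocol article*

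**What the plan says.** **How the document is made and filed.** Intervention description says PROMs are scored automatically and the scores are "represented graphically (along with prior PROM scores) in a downloadable summary document". The next step belongs to staff: "The summary document will be imported into the patients’ EHR by the intake coordinator for the service".

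**What the all-patient extract contains.** Under Data collection, the EHR data listed for all patients are the total number of encounters and two document counts. One is "the number of patients who have the PROMs summary document in their EHR (by service". The other is taken per timepoint: "the number of patients who have the PROMs summary document at intake, midpoints of treatment and discharge". No record of PROM completion as such is listed.

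**How the analysis names the result.** Under the de-identified EHR data heading of Data analysis, the penetration rule reads "the percentage of patients participating in MBC (i.e., filling out PROMs) will be calculated using the total number of patients enrolled in the services". That total is then "compared with the number of patients who responded to PROMs". A further sentence covers the schedule: "The percentage of patients filling out PROMs at intake, midpoint and discharge will also be calculated (as a measure of fidelity and penetration".

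**Other relevant sources.** Data collection also plans an MBC PROMs database that gives completion at planned timepoints, restricted to patients and caregivers who consent to research use. The same section assigns fidelity questions to the staff survey, the clinician interviews and the focus groups.

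**The concern.** The quantity collected and the quantity reported differ. A document is present only if two things happened: the PROM was completed in the collection platform, and the intake coordinator imported the summary. The analysis wording refers to the first event alone. Any failure of the second is charged to the patient or caregiver.

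This matters because the evaluation is formative. It is meant to find and remove barriers to collecting and using PROMs. Low completion points towards burden, access or engagement among patients and caregivers; low import points towards staff workflow. A single percentage that merges the two, under a label describing patient behaviour, could direct the improvement work to the wrong place. Potential issues for this study also expects operational processes to change quickly after opening, so a change in import practice could be read as a change in patient uptake.

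**Working it through.** The article states no completion rate, import rate or target for this count, so there is no figure of its own to reproduce. The check is a comparison of sections, followed by an illustration under assumed rates.

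**Step 1: trace the numerator.**

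| Stage | Who acts | Where described | In the all-patient extract as listed? |
|---|---|---|---|
| PROM completed | Patient or caregiver | Intervention description | No |
| Scored, summary produced | Platform, automatic | Intervention description | No |
| Summary imported into EHR | Intake coordinator | Intervention description | Yes, as document present |
| Reported result | – | Data analysis | Named as patients filling out or responding to PROMs |

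The extract observes the third stage; the report names the first.

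**Step 2: direction and size.** Let c be the proportion of patients who completed a PROM and m the proportion of those completers whose summary is in the EHR. Both are taken at the level being reported: any document for the overall figure, that timepoint's document for the timepoint figures. Assume no document exists without a completed PROM. Then:

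- reported percentage = c × m
- shortfall = c − c × m = c × (1 − m)

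Under that assumption the error is never upward.

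**Step 3: illustration with assumed rates.**

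| Assumed completion c | Import m | Reported c × m | Shortfall c × (1 − m) |
|---|---|---|---|
| 80% | 100% | 80% | 0 points |
| 80% | 95% | 76% | 4 points |
| 80% | 90% | 72% | 8 points |
| 80% | 80% | 64% | 16 points |
| 60% | 95% | 57% | 3 points |
| 60% | 90% | 54% | 6 points |
| 60% | 80% | 48% | 12 points |

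**Step 4: can the extract separate the two causes?** No. A reported 64% fits 80% completion with 80% import (0.80 × 0.80 = 0.64) as well as 64% completion with complete import (0.64 × 1.00 = 0.64).

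**Step 5: does another planned source separate them?** In part. The MBC PROMs database records completion directly, but only for consenters. Participants and recruitment says walk-in patients are not asked for data-use consent at their visit, and Potential issues for this study accepts that not everyone will consent. The article does not say that the database and the EHR count will be compared.

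**The case against.** **Document presence is a defensible penetration measure.** Clinicians are to view scores in the EHR, so a PROM that was never imported did not reach the encounter as designed. This stands as a reason to keep the count. It does not justify calling it patients filling out PROMs.

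**The database already measures completion.** It does, for consenters. It is a partial check, thinnest for walk-in patients, and no comparison is stated.

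**Import problems may surface elsewhere.** Support staff have their own version of the survey and administrative staff are sampled for interview. Those sources may reveal that imports fail, but they will not correct the percentage.

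**Details may sit in the supplementary evaluation plan.** That is a fair answer to any complaint about a missing breakdown by instrument or respondent, or a missing definition of adoption, and neither is pressed here. It does not answer the mismatch, because the article itself fixes both the numerator and its interpretation.

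**A stronger reading on fidelity.** MBC is defined in three steps, ending with "3) collaborative re-evaluation of the treatment plan informed by data", while the timepoint percentages reflect only the first. A reader might infer that a centre filing every PROM and reviewing none would score full fidelity. The article does not support that. It calls the percentages one measure of fidelity, and the survey, clinician interviews and focus groups are also assigned fidelity, the last two expressly asking about use and discussion of PROMs in encounters.

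**A stronger reading on size.** A reader might infer a large bias, for example 24 points at 80% completion and 70% import (0.80 × 0.30 = 0.24). Both rates would be assumed. That the import is done by hand is likewise an inference from the downloadable file and the coordinator's role.

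**Conclusion.** The point holds as a mismatch between what is counted and what is reported. Followed as written, the only penetration figure covering all patients understates completion by c × (1 − m) and merges two barriers that the evaluation needs to tell apart. The size is unknown: at an assumed 80% completion it is 4 points with 95% import and 16 points with 80% import, and it disappears if every summary is imported. The result rests on the import being a separate staff step, as Intervention description states, and on no document existing without a completed PROM.

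On fidelity, only a labelling point remains: the timepoint percentages describe administration, the first MBC step. The plan does not reduce fidelity to that step.

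**What to change.** 1. In Data analysis, label the EHR percentage *summary document available in the EHR*, not patients filling out or responding to PROMs.
2. Describe the timepoint percentages as *fidelity of administration (MBC step 1)*, and say that review and use are covered by the survey, interviews and focus groups already planned.
3. Report completion separately from import. At minimum, among research consenters, cross-tabulate completion in the MBC PROMs database against document presence in the linked EHR, by timepoint and service. The completed-but-not-imported cell then becomes a result in its own right.
4. Where research-access policy permits, add aggregate de-identified completion counts from the platform for all patients, including walk-in.

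**Cost.** Items 1 and 2 are wording changes. Item 3 is a small extra analysis and needs document presence carried as a field in the linked data, which the article's list of EHR variables to be matched does not name. Item 4 is an extra data request; Potential issues for this study says data access is controlled by research policies, and the article does not say whether aggregate counts fall outside the consent requirement. If item 4 is refused, the import rate will come from consenters only and may not represent non-consenters or walk-in patients. The report should say so.
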